**8-3-2 Reference document to define the expected character of an SAE**

NA

**8-3-3-3 List of expected adverse reactions**

Adverse reactions that can be experienced with the spa therapy are rare, most often minor and transient. They are traditionally observed during the period of the spa therapy and are then part of what is usually called the "thermal crisis": tiredness, waking up of some of the usual pain, unusual sweating and insomnia. These effects rarely require the cessation of spa therapy. More serious health problems are possible but remain exceptional: heart problems, bacterial infections that may be present in warm waters (including Legionella infection).

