**4.4. EXPERIMENTAL DRUGS / MEDICAL TREATMENTS UNDER STUDY**

NA

**4.5. EXPECTED DURATION OF PARTICIPATION OF PERSONS AND DESCRIPTION OF THE CHRONOLOGY AND DURATION OF ALL TRIAL PERIODS, INCLUDING FOLLOW-UP, IF NECESSARY.**

Inclusion visit

The investigating physician verifies that the patient meets the inclusion criteria defined in advance, during a consultation carried out in the rheumatology department of Nancy University Hospital, Vandoeuvre les Nancy.

This physician will ensure that the patient has a knee X-ray performed according to current recommendations to verify the eligibility criteria. If necessary, a digitized radiograph will be taken in the rheumatology department.

After randomization, the investigating physician gives the eligible patient the information form that corresponds to the type of cure selected and obtains his/her consent to enter the study.

A plan is given to the patient.

Follow-up visits

Subsequent visits will all take place at the Nancy Thermal site in the spa center. They will involve the thermal physician and/or the assessor who will collect the data necessary for the study (V0, V1, V2, V3 and V4) (see monitoring table). The thermal physician also ensures the medical follow-up of the treatment and collects adverse reactions.

Occupancy, group planning:

This study will be conducted from mid-March to mid-December 2012. The flow of patients has been planned for both types of treatment: "classic spa therapy", “active spa therapy". A subgroup will consist of a maximum of 8 patients. Over 6 weeks and for each type of spa therapy, 4 subgroups can be included, i.e., 32 patients randomized in each group (64 patients). The study will focus on 5 cycles of 6 weeks for a total time of 30 weeks.

In the morning, the premises, care and carers will be dedicated to the "classic spa therapy" group, i.e., a daily occupation over 3 consecutive weeks for 2 subgroups of patients or over 6 weeks for 4 subgroups of patients.

In the afternoon, the premises, care and carers will be dedicated to the group “active spa therapy" for 3 weeks of usual spa therapy, then 3 weeks of rehabilitation/education by alternating sub-groups on alternate days, i.e., a daily occupation over 6 weeks for 4 subgroups.

This organization will allow for the same premises for both groups ("classic spa therapy" and “active spa therapy") while avoiding that they are in close contact, comparing their care while avoiding shifting the groups over time.

Coordination

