**8.3 PROCEDURES IN PLACE FOR THE REGISTRATION AND NOTIFICATION OF ADVERSE EVENTS**

**8-3-1 Definitions**

An adverse event is a harmful event that occurs in a person who is engaged in biomedical research, whether this person is related or not to the research or product to which this research relates.

An adverse reaction is a harmful and unintended reaction to an experimental drug, occurring at the normal dosage used in humans.

A serious adverse event (SAE) or serious adverse reaction is an event or effect that may have contributed to the patient's death, life-threatening event, hospitalization or prolongation of hospitalization, incapacity or significant disability, or lasting disability, or result in a congenital anomaly or malformation.

The list of expected adverse events related to the study is based on of the registration document.

An SAE is unexpected when it is not on this list.

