**8-3-4 Transmission of SAE**

As soon as an investigator becomes aware of a SAE or a new event, he/she shall declare this without delay to the promoter by faxing the SAE declaration form at [name].

- If it is an unexpected serious adverse reaction or a event, the sponsor will contact the investigator to write a report, which will be forwarded to the AFSSaPS, CPP and EUDRAVIGILANCE within 7 days in the event of death or vital prognosis, if not within 15 days.

When the event is not resolved on the date the fax is sent, the investigator is required to send a supplementary report to document the evolution or update missing data.

- An expected SAE will be collected by the sponsor for the preparation of annual safety reports.

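### Serious spa-related cardiac problems and waterborne infections count as expected, so their prompt reporting to the authorities and ethics committee is not assured

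*Protocol*

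**What the plan says.** Section 8-3-1 (Definitions) sets the test: "An SAE is unexpected when it is not on this list". It gives the source of the list as follows: "The list of expected adverse events related to the study is based on of the registration document". The next section, headed "Reference document to define the expected character of an SAE", contains only NA. Section 8-3-1 also defines an adverse reaction as a response to an experimental drug, whereas Section 4.4, on experimental drugs and treatments, says NA.

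The list itself is in Section 8-3-3-3, under the title "List of expected adverse reactions". It begins with the mild and passing effects of the so-called thermal crisis and then adds: "More serious health problems are possible but remain exceptional: heart problems, bacterial infections that may be present in warm waters (including Legionella infection".

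Section 8-3-4 gives the routes. The investigator declares every SAE to the sponsor without delay. The expedited route, with deadlines of 7 days for fatal or life-threatening cases and 15 days otherwise, to AFSSaPS, the CPP and EUDRAVIGILANCE, opens with: "If it is an unexpected serious adverse reaction or a event, the sponsor will contact the investigator to write a report". For the rest: "An expected SAE will be collected by the sponsor for the preparation of annual safety reports". Section 8.6 sends the annual safety reports to AFSSaPS and the CPP and does not say when the year begins.

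On timing, Section 4.5 states: "This study will be conducted from mid-March to mid-December 2012".

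**The concern.** The list names the gravest hazards of the intervention without any limit of severity or outcome. Because being listed is all it takes to be expected, a fatal infarction attributed to the spa care, or a Legionella death, would be handled in the same way as transient tiredness that happened to meet the SAE definition.

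This matters more here than in many trials because the exposure is shared. Both arms use the same premises (Section 4.5) and take group pool sessions (Section 6.1). The site does not yet have thermal approval (Summary, differences from usual care), and its bacteriological sampling was still under way (Section 6, course of the spa therapy). One waterborne infection may therefore bear on patients in later cycles, and the authority and ethics committee would have an interest in learning of it while those cycles could still be affected.

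**Working it through.** **Routing.** Take a serious case of Legionella infection, or a cardiac problem, that is attributed to the spa care.

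1. Is it on the list? Yes. Section 8-3-3-3 names both.
2. Is it unexpected? No. Section 8-3-1 has no criterion other than absence from the list; severity, outcome and frequency play no part.
3. Which route applies? Under Section 8-3-4, the annual report. The expedited route is tied to an unexpected serious adverse reaction. Its second limb is garbled: it might mean the new event mentioned in the sentence before it, but that term is not defined and is not applied to listed reactions.

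The supporting text does not settle the matter. Section 8-3-1 rests the list on a document that Section 8-3-2 does not identify, and the definition of adverse reaction refers to a drug that this trial does not use.

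**Timing.** The inputs are:

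- Section 4.5: treatment from mid-March to mid-December 2012; 5 cycles of 6 weeks; 64 patients per cycle; inclusion from January 2012; study start December 2011.
- Section 9: 284 patients.
- Summary: protocol version date 20 October 2011.

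The plan's own figure reproduces: 5 × 6 = 30 weeks. Capacity is 5 × 64 = 320 places, which covers the 284 planned.

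Taking mid-month as the 15th, treatment runs from 15 March to 15 December 2012, which is 275 days or 275/7 = 39.3 weeks. Thirty consecutive weeks from 15 March would end on 11 October 2012.

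The start of the annual clock is an assumption, so a range is shown. First report = clock start + 12 months. Wait = first report − 15 March 2012, for an event on the first treatment day.

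| Assumed clock start | First annual report | Against 15 Dec 2012 | Against 11 Oct 2012 | Wait |
| --- | --- | --- | --- | --- |
| Protocol date, 20 Oct 2011 | 20 Oct 2012 | 56 days before | 9 days after | 219 days |
| Study start, 1 to 31 Dec 2011 | 1 to 31 Dec 2012 | 14 days before to 16 after | 51 to 81 days after | 261 to 291 days |
| First inclusion, 1 to 31 Jan 2012 | 1 to 31 Jan 2013 | 17 to 47 days after | 82 to 112 days after | 292 to 322 days |
| First treatment, 15 Mar 2012 | 15 Mar 2013 | 90 days after | 155 days after | 365 days |

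The shortest wait is 219/7 = 31.3 weeks, against 7 or 15 days on the expedited route. A later event that still falls before the first report waits less.

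**The case against.** Four points on the other side carry weight.

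- *Oversight does not disappear.* A reader might infer that later cycles would run with no outside review. The documents do not support that. Every SAE goes to the sponsor without delay (Section 8-3-4), the steering committee monitors undesirable events during the study (Section 8.5.1), and a supervisory committee of people outside the research can be consulted (Section 8.5.2). That committee acts only when the sponsor calls on it, so outside review is available but not assured.
- *The trigger is ambiguous.* A reader might infer that a listed fatal event certainly has no 7-day route. Because of the garbled second limb, the text supports only that the route is unclear at best.
- *The annual clock is not fixed.* A reader might infer that all patients will have been treated before the authorities hear of a listed event. That holds for some starting points, is borderline for a December 2011 start, and fails against the mid-December end for a clock running from the protocol date.
- *Events are not reactions.* The list concerns reactions to spa therapy, and the remark that serious ones are exceptional describes those only. It does not describe the background rate of cardiac admissions in patients with knee osteoarthritis. Expediting every cardiac SAE regardless of cause would therefore go beyond the problem, at a cost the documents do not allow one to estimate.

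It can also be said that the drug-based definition is template wording, that Sections 8.1 and 8-3-3-3 plainly apply the term to spa care, and that the list is usable because it is printed in full. That is fair: these inconsistencies are secondary. Whether regulation permits serious events to be listed as expected cannot be judged from the documents, and the point does not depend on it.

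None of this removes the stated rule that sends a listed serious reaction to the annual report.

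**Conclusion.** The point stands as a defect in what the protocol says. Under its literal wording, a serious or fatal spa-related cardiac problem or waterborne infection is expected, and its only clear path to AFSSaPS and the CPP is the annual safety report. What is lost is assured prompt reporting to those two bodies; the sponsor is informed at once.

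The delay depends on a clock that the protocol does not fix. Over the starting points considered, the first report falls between 56 days before and 90 days after mid-December 2012, and an event on the first treatment day waits 219 to 365 days. These figures assume mid-month means the 15th and that the report issues exactly 12 months after the clock starts. The routing conclusion needs neither assumption. The correction should be made, but as a matter of reporting wording; it does not show that patients would be left unsupervised.

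**What to change.** Reconcile Sections 8-3-1 to 8-3-4:

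1. Either keep only the non-serious thermal-crisis effects on the expected list, or state that a cardiac event or waterborne infection that meets the SAE definition and is suspected to be related to the study care is not treated as expected, follows the existing 7/15-day route and is copied to the supervisory committee.
2. Rewrite the expedited trigger in Section 8-3-4 so that its second limb has a defined meaning.
3. Define adverse reaction in terms of the spa and rehabilitation care instead of an experimental drug.
4. Identify the document on which the list rests, or remove the reference, so that Sections 8-3-1 and 8-3-2 agree.

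The cost is protocol wording plus a small number of additional expedited reports. The relatedness condition limits that number, since it keeps unrelated cardiac admissions out and the protocol itself regards serious spa-related problems as exceptional.

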**8-3-4 Transmission of SAE**

As soon as an investigator becomes aware of a SAE or a new event, he/she shall declare this without delay to the promoter by faxing the SAE declaration form at [name].

- If it is an unexpected serious adverse reaction or a event, the sponsor will contact the investigator to write a report, which will be forwarded to the AFSSaPS, CPP and EUDRAVIGILANCE within 7 days in the event of death or vital prognosis, if not within 15 days.

When the event is not resolved on the date the fax is sent, the investigator is required to send a supplementary report to document the evolution or update missing data.

- An expected SAE will be collected by the sponsor for the preparation of annual safety reports.

**8-3-5 Transmission of non-serious adverse reactions**

These will be briefly described by the investigator on the summary sheet dedicated to this end.

**8.4. MODALITIES AND DURATION OF FOLLOW-UP OF PERSONS FOLLOWING THE OCCURRENCE OF UNDESIRABLE EVENTS**

When a serious adverse event persists, including after the end of the study, the investigator will follow the patient until the event is considered resolved and will forward the follow-up data to the appropriate body.

**8.5. SPECIFIC RESEARCH COMMITTEES**

**8.5.1 STEERING COMMITTEE**

[name], [name], [name], [name], [name], [name], [name], [name].

It will define the general organization and conduct of the research and will coordinate the information. It will initially determine the methodology and decide during the research process procedures to be followed in unforeseen cases and will monitor the progress of the research in particular in terms of tolerance and undesirable events.

**8.5.2 INDEPENDENT SUPERVISORY COMMITTEE – DATA SAFETY MONITORING BOARD**

[name], [name] (Methodologist), [name], [name]

An independent Supervisory Committee has an advisory and decision-making function when called upon by the proponent on medical issues such as tolerance and adverse events. It consists of people from outside the research, necessarily one of whom is a clinician specializing in the pathology studied and a pharmacologist/pharmacovigilant and according to the protocol a methodologist/biostatistician.

**8.5.3 INDEPENDENT CRITICAL EVENT EVALUATION COMMITTEE**

NA

**8.6 SAFETY REPORTS**

- Annual Safety Reports: the sponsor prepares the annual safety reports and forwards them to the AFSSaPS, CPP. The coordinating investigator will forward to the sponsor all the data necessary for the preparation of this report.

- Final report: written by the sponsor and the coordinating investigator within 1 year after the end of the study. All investigators are informed of the results of the study. A summary is sent to the AFSSaPS by the promoter.

**9. STATISTICS**

**Number of subjects required**

- Main objective: with a 50% percentage of responders to standard spa therapy at 6 months [1], a power of 80%, and an alpha risk of 5%, 135 patients per group are required to significantly demonstrate the non-inferiority of the active spa therapy with a lower confidence limit of the difference in proportions of 15%. Considering that the number of patients lost to follow up may be limited to 5%, a total of 284 patients should be included in the trial.
- For the secondary objective of comparing 3-month responders, the percentage of responders being higher than at 6 months, the number of subjects needed is lower: with a 60% percentage of responders to standard spa therapy at 3 months, a power of 80%, an alpha risk of 5%, 77 patients per group are required to significantly demonstrate the non-inferiority of the active spa therapy with a lower confidence limit of the difference in proportions of 19%. For demonstrating an effect of spa therapy sufficient to obtain thermal approval, the evidence of an effect size of 0.3 in an analysis of the before-and-after effect in the same group [6] with 80% power and 5% alpha risk with a test, 90 patients are needed in each group.

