**Comparison of groups**

The trial being a non-inferiority trial, the main analysis will be per protocol to be conservative by increasing the contrast between the groups.

Main objective

The active spa therapy will not be considered inferior to the standard spa therapy if the lower bound of the confidence interval at 90% of the difference between the 2 groups (active spa therapy minus standard spa therapy) for the main outcome criterion (percentage of respondents according to the composite criterion) is not less than 15%[1]. After verification of the randomization that could be unbalanced owing to the Zelen randomization mode, the final analysis will be adjusted if necessary on the variables that differ between the 2 groups.

Secondary objectives

- The same analyses will be repeated for the MCII composite criterion, pain and function at 3 months and for PASS criteria.

- To determine the predictive factors of spa therapy response, a bivariate analysis will be performed using chi-square tests (or Fisher exact tests depending on the number) for discrete variables, and Student t-tests, ANOVA or Wilcoxon tests for quantitative variables. The parameters significant on bivariate analyses (at the conservative threshold of p=0.1) will then be introduced into a stepwise multiple logistic regression.

A value of p<0.05 will be considered statistically significant.

The statistical analysis will be carried out by the Centre for Clinical Epidemiology by using SAS v9.2 (SAS Inc., Cary, NC).

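### The 3-month non-inferiority comparison is sized on an unexplained 19-point margin while the analysis section carries over a 15-point rule, and the stated 77 per group does not follow from its own inputs

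*Protocol*

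**What the plan says.** In section 9 of the protocol, under Number of subjects required, the 6-month comparison is sized "with a lower confidence limit of the difference in proportions of 15" per cent, with 50% responders, 80% power and 5% alpha. This gives 135 per group and 284 in total after a 5% allowance for loss.

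The next bullet turns to 3 months. It says that, "the percentage of responders being higher than at 6 months, the number of subjects needed is lower". Its inputs are "with a 60% percentage of responders to standard spa therapy at 3 months", then "a power of 80%, an alpha risk of 5%, 77 patients per group are required", and the margin is introduced "with a lower confidence limit of the difference in proportions of 19" per cent. No reason is given for moving from 15 to 19 points.

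Under Comparison of groups in the same section, the decision rests on "the lower bound of the confidence interval at 90% of the difference between the 2 groups", active minus standard, with a threshold of 15%. For the secondary objectives the text then says: "The same analyses will be repeated for the MCII composite criterion, pain and function at 3 months and for PASS criteria". The statistical row of the protocol summary repeats this arrangement. The 19-point figure appears only in the sample-size bullet.

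**The concern.** Two passages of one section point to different thresholds for the same 3-month comparison. If the 3-month lower bound fell between -19 and -15 points, the sample-size text would support non-inferiority and the analysis text would not.

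The sample-size sentence has two further weaknesses. It explains the smaller number by the responder rate alone, although the margin changed in the same step. And 77 looks too small for the inputs printed beside it.

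What is at stake is the reading of one secondary claim and the accuracy of one stated sample size. The primary analysis is not involved.

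**Working it through.** **Inputs.** All come from section 9 of the protocol. Responders under standard therapy are 50% at 6 months and 60% at 3 months. Power is 80% and alpha 5%. The margin in the sample-size text is 15 points at 6 months and 19 points at 3 months. I take alpha as one-sided 5%, because the rule uses the lower bound of a 90% interval. I take equal true rates in the two arms, because no other difference is stated, and I read the 15% threshold as -15 points.

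**Formula.** Unpooled normal approximation, per group:

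n = (1.645 + 0.8416)² × 2p(1 − p) / m²

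**Plan's 6-month figure first.** p = 0.50, m = 0.15: n = 137.4, so 138. The Farrington-Manning score method gives 135.3, so 136. The plan states 135, which reproduces closely.

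**3-month figure with its own inputs.** p = 0.60, m = 0.19: n = 82.2, so 83. Other methods:

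| Method | Per group |
| --- | --- |
| Farrington-Manning | 81 (80.5 before rounding) |
| Exact enumeration of the 90% Wald-interval rule | 80% power first passed at 81 among the sizes checked |
| Unpooled variance at the margin | 83 |
| Pooled | 85 (95 with continuity correction) |
| Arcsine | 85 |
| Continuity-corrected non-inferiority | 93 |
| Unpooled, one-sided 2.5% | 105 |

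Taking the 19 points upward (60% against 79%) gives 70 to 72, or 82 with continuity correction. None of these gives 77. About 66% responders at 19 points, or 50% at 20 points (77.3 before rounding), would come close, but the protocol states neither.

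**Power at 77 per group, 60% responders, 19 points.** The standard error is √(0.48/77) = 0.0790. Power is Φ(0.19/0.0790 − 1.645) = 77.7%. Farrington-Manning gives 78.5% and exact enumeration 77.3%.

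**Where the reduction comes from (unpooled formula).**

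- 50% to 60% responders at 15 points: 137.4 to 131.9, a fall of 5.5.
- 15 to 19 points at 60% responders: 131.9 to 82.2, a fall of 49.7.
- Total: 55.2, of which the responder rate explains about one tenth.

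**What the planned size supports at 3 months, 60% responders.**

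- 135 per group, 15 points: Φ(0.15/√(0.48/135) − 1.645) = 80.8%.
- 135 per group, 19 points: 93.8%.
- 131 per group, 15 points: 79.8%. Since n = 131.9 is needed for 80%, power slips below 80% once fewer than 132 per group are evaluable.
- 284 patients are 142 per group, so 132 leaves room for 10 losses or exclusions per group (10/142 = 7.0%).

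**The case against.** The strongest reply is that the analysis text attaches 15% to the main outcome criterion. Repeating the same analyses could mean the same method (90% interval, per protocol), with the 3-month margin taken from the sample-size bullet. That reading is possible, so this is an ambiguity to be reconciled more than a flat contradiction. It remains an ambiguity in the protocol's own text, because the analysis section names no other margin. A statistical analysis plan that is not shown may settle it, so nothing here shows that the margin would be chosen after seeing the data.

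It is also fair to say that the responder rate is offered as the reason for the lower number, not for the wider margin, and that its direction is right: 60% needs slightly fewer patients than 50%. A reader might infer that the margin was given a false justification. The text does not say that. The margin has no stated justification, and the reason given for the number is true but small.

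A reader might also infer that 19 points would give away the whole benefit of spa therapy. Converting the effect size of 0.42 from section 2 to responders through an assumed latent normal scale gives about 16.6 points at 60% responders, but 11.9 to 19.7 points for effect sizes of 0.3 to 0.5. That range contains 19, and its lower end lies below 15, so it does not single out 15 as sound. Relative to the stated control rates the two margins are close: 15/50 = 30% and 19/60 = 32%.

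Finally, the shortfall is 4 to 6 patients per group, and 77 sizes nothing, because enrolment is set by the main objective. That stands and limits the severity.

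**Conclusion.** The point holds as a correction to a secondary objective. The 15- and 19-point passages must be reconciled, because a lower bound between them has two possible conclusions. The stated 77 should be about 81 to 83, and 77 give about 78% power instead of 80%. The explanation for the lower number is misleading, since about 50 of the 55-patient fall in the computed number comes from a margin change that the text does not explain.

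This rests on one-sided 5%, equal true rates and the -15 reading of the threshold. The 6-month figure reproduces under the same assumptions.

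Two further inferences are not supported. The trial is not underpowered at 3 months: the planned 135 per group give about 81% power at 15 points and 94% at 19. Nor can the chance of passing the 19-point rule when active therapy is truly 15 points worse be called a false-positive rate, because under a 19-point margin such a deficit counts as non-inferior.

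**What to change.** State a single 3-month margin before analysis. The simplest choice is the 15 points that the analysis section already carries. Then replace the 77-per-group sentence by: *With 60% responders, 135 evaluable patients per group give about 81% power for a 15-point margin (one-sided 5%).* Add that power falls just below 80% if fewer than about 132 per group are evaluable per protocol.

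If 19 points is kept, the analysis section must name it for 3 months and justify it, and 77 must become about 81 to 83. The sample-size text should then attribute the smaller number mainly to the wider margin. The remark that a higher responder rate lowers the requirement may stay if its small size is made clear.

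Either way the cost is wording only. The 284 patients and the primary analysis do not change.
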